### **14.1.1 Safety Follow-Up Procedures for participants with ALT $\geq$ 3xULN and bilirubin $\geq$ 2xULN (>35% direct)**

This event is considered an SAE (see Section 13.1.2). Serum bilirubin fractionation should be performed if testing is available. If fractionation is unavailable, urinary

bilirubin is to be measured via dipstick (a measurement of direct bilirubin, which would suggest liver injury).

- Make every reasonable attempt to have the participants return to the clinic (within 24 hours) for repeat liver chemistries, additional testing and to be monitored closely (with specialist or hepatology consultation recommended).
- Monitor participants twice weekly until liver chemistries (ALT, AST, alkaline phosphatase, bilirubin) resolve, stabilize or return to within baseline values.

**14.1.2 Safety Follow-Up Procedures for participants with ALT  $\geq$  5xULN or ALT  $\geq$  3xULN who have hepatitis symptoms or rash, can't be monitored for 4 weeks or have elevations that persist  $\geq$  4 weeks [Stopping Criteria section 10.5]:**

- Make every reasonable attempt to have the subject return to the clinic within 24-72 hours for repeat liver chemistries and additional testing.
- Monitor participants weekly until liver chemistries (ALT, AST, alkaline phosphatase, bilirubin) resolve, stabilize or return to within baseline values.

**14.1.3 Safety Follow-Up Procedures for participants with ALT  $\geq$  3xULN and  $<$  5xULN and bilirubin  $<$  2xULN, who do not exhibit hepatitis symptoms or rash:**

- Notify the medical monitor within 24 hours of learning of the abnormality to discuss participant safety.
- Participant can continue IMP if liver chemistries (ALT, AST, alkaline phosphatase, bilirubin) can be monitored weekly for up to 4 weeks.
- If at any point these participants meet the liver chemistry stopping criteria (outlined in Section 10.5), immediately withdraw IMP, perform additional testing and continue safety follow-up until liver chemistries resolve, stabilize or return to baseline values.
- After 4 weeks of monitoring, if ALT  $<$  3xULN and bilirubin  $<$  2xULN, participants must be monitored twice monthly until liver chemistries normalize or return to within baseline values.

**14.1.4 Recommended additional Follow-Up Procedures for participants who meet *any* of the stopping criteria:**

- Viral hepatitis serology including:
  - Hepatitis A IgM antibody;
  - Hepatitis B surface antigen and Hepatitis B Core Antibody (IgM);
  - Hepatitis C RNA;
  - Cytomegalovirus IgM antibody;
  - Epstein-Barr viral capsid antigen IgM antibody (or if unavailable, obtain heterophile antibody or monospot testing);
  - Hepatitis E IgM antibody.
- record the time of the last dose
- Serum creatine phosphokinase (CPK) and lactate dehydrogenase (LDH).
- Fractionated bilirubin, if total bilirubin  $\geq$  2xULN.
- Assess eosinophilia

- Record the appearance or worsening of clinical symptoms of hepatitis (fatigue, nausea, vomiting, right upper quadrant pain or tenderness, fever, rash or eosinophilia) as relevant on the AE CRF
- Record use of concomitant medications, paracetamol, herbal remedies, other over the counter medications, or putative hepatotoxins on the Concomitant Medications CRF.
- Record alcohol use on the Liver Events eCRF.

The following are required for participants with ALT  $\geq$  3xULN **and** bilirubin  $\geq$  2xULN (>35% direct) but are optional for other abnormal liver chemistries:

- Anti-nuclear antibody, anti-smooth muscle antibody, Type 1 anti-liver kidney microsomal antibodies and quantitative total immunoglobulin G (IgG or gamma globulins).
- Serum paracetamol adduct HPLC assay (quantifies potential paracetamol contribution to liver injury in participants with definite or likely paracetamol use in the preceding week).
- Liver imaging (ultrasound, magnetic resonance, or computerized tomography) to evaluate liver disease.
- The Liver Imaging and/or Liver Biopsy eCRFs are also to be completed if these tests are performed.

The procedures listed below are to be followed if a subject has ALT, bilirubin and/or INR elevations that meet the definition of an SAE (as defined in Section 13.1.2):

- Notify the medical monitor within 24 hours of learning of the abnormality to confirm follow-up.
- Complete the liver event eCRFs.
- Upon completion of the safety follow-up withdraw the subject from the trial unless further safety follow up is required.
- Make every reasonable attempt to have participants return to the clinic within 24 hours for repeat liver chemistries, additional testing, and close monitoring (with specialist or hepatology consultation recommended).
- Monitor participants twice weekly until liver chemistries (ALT, AST, alkaline phosphatase, bilirubin) resolve, stabilize or return to within baseline values.
- Obtain viral hepatitis serology including:
  - Hepatitis A IgM antibody.
  - Hepatitis B surface antigen and Hepatitis B Core Antibody (IgM).
  - Hepatitis C RNA.
  - Cytomegalovirus IgM antibody.
  - Epstein-Barr viral capsid antigen IgM antibody (or if unavailable, obtain heterophile antibody or monospot testing).
  - Hepatitis E IgM antibody.
- Serum creatine phosphokinase (CPK) and lactate dehydrogenase (LDH).
- Assess eosinophilia
- Record the appearance or worsening of clinical symptoms of hepatitis (fatigue, nausea, vomiting, right upper quadrant pain or tenderness, fever, rash or eosinophilia) on the AE CRF.

- Record use of concomitant medications, paracetamol, herbal remedies, other over the counter medications, or putative hepatotoxins on the Concomitant Medications CRF.
- Record alcohol use on the Liver Events CRF.
- Anti-nuclear antibody, anti-smooth muscle antibody, Type 1 anti-liver kidney microsomal antibodies and quantitative total immunoglobulin G (IgG or gamma globulins).
- Serum paracetamol adduct HPLC assay (quantifies potential paracetamol contribution to liver injury in patients with definite or likely paracetamol use in the preceding week)
- Liver imaging (ultrasound, magnetic resonance, or computerized tomography) to evaluate liver disease.

The Liver Imaging and/or Liver Biopsy eCRFs are also to be completed if these tests are performed

## **15 Evaluation of Results**

### **Primary:**

Change in vascular inflammation (using derivatives of Standard Uptake Value (SUV) and Tissue to Background Ratio (TBR) in the carotid and aortic arteries of patients following 16 weeks of treatment.

Change in flow mediated dilatation following 16 weeks treatment.

Change in atheromatous plaque and vessel wall characteristic using MRI and/or FDG-PET/CT, following 16 weeks of treatment. MRI analysis will be dependent on a sufficient number of datasets since this was an optional sub-study. In the case of insufficient datasets the MRI primary endpoint will not be analysed and reported in the primary analysis of this clinical trial, and may be included as an exploratory analysis. A minimum of 85% of paired MRI scans (i.e. pre and post dose in the same patient) of all the MRI scans performed in this sub-study will be deemed to be sufficient. The scans will need to be of high image quality, and without any technical issues which preclude analysis (e.g. patient movement, ECG gating etc.).

### **Secondary:**

Change in lung inflammation assessed by FDG-PET/CT, following 16 weeks of treatment.

Change in visceral and subcutaneous fat inflammation, and serum/plasma measures of systemic inflammation, following 16 weeks of treatment.

Change in arterial stiffness measures (aortic pulse wave velocity and augmentation index), following 16 weeks of treatment.

Change in baseline corrected blood concentration of biomarkers.

Change in spirometry (FEV1, FVC, FEV1/FVC ratio), sniff nasal inspiratory pressures and 6MWT following 16 weeks of treatment.

Change in body composition as measured by body mass index (BMI) and free fat mass index (FFMI), following a 16 week treatment.

Safety and tolerability parameters, including physical examination, blood pressure, heart rate, 12-lead electrocardiogram (ECGs) recordings, clinical laboratory tests, lung function, and adverse event reporting

## **16 Statistics**

### **16.1 Statistical methods**

The primary focus of the trial is the quantification of vascular inflammation using the PET/CT images. From such images a Standard Uptake Value (SUV) and a Tissue to Blood Ratio (TBR) (both measures of FDG uptake) will be calculated using dedicated software.

Subsequent manipulation and interpretation of the TBR/SUV data is not well established and will be open to revisions based on the data observed. It is hypothesized that Losmapimod acts only on tissue that is already inflamed, hence the interpretation aims to focus only on inflamed tissue, but the identification and tracking of such tissue between the observations is subjective.

The identification will be performed by trained trial staff using Osirix software to trace the border of each vessel/section within each slice. See the Imaging section within the TPM for further operational details. From each slice and vessel/section identified, a maximum and mean SUV and TBR value will be calculated over the associated region of the slice by the software. These values will be referred to as max-SUV, mean-SUV, max-TBR and mean-TBR respectively.

Within each participant visit the vessel with the highest number of slices with max-TBR > 1.6 will be identified within each participant at the initial visit and subsequently followed. This will be termed the "index vessel".

Within each vessel and participant visit the following variables will be derived from either for each vessel and also for the index vessel:

1. Maximum value over all slices for max-SUV, mean-SUV, max-TBR & mean-TBR
2. Mean value over all slices for max-SUV, mean-SUV, max-TBR & mean-TBR: The whole vessel means.
3. Incidence of slices with max-TBR > 1.6
4. Incidence of slices with mean-TBR > 1.6
5. The mean of the max-TBR value over the five contiguous slices centred on the slice with the highest max-TBR in the vessel: the most diseased segment mean of max-TBR.

For all derived variables considered, summary statistics of the post-treatment values and change from baseline will be presented broken down by treatment group. Summary statistics for continuous endpoints are n (number of observations), mean, sd, median, minimum, maximum. Summary statistics for incidence or categorical variables are percentage, count and n – p% (x/n).

Formal ANCOVA analysis will be performed on the change from baseline, with fixed effects for the treatment and adjustment for baseline value and treatment centre. Estimates of the treatment effect, (Losmapimod – Placebo) will be provided with 95% confidence intervals and p-values. All estimated regression parameters will be reported in a similar fashion. Comparisons of proportions will be handled using a similar approach based on logistic regression to estimate odd ratios.

As an exploratory trial the focus will be estimation and interpretation of treatment effects and not on formal hypothesis tests. As such no adjustment for the extensive multiple testing will be done.

Secondary endpoints will have similar summary measures reported broken down by time-point and treatment group. Endpoints that are repeatedly observed in the intermediate visits during treatment will be summarised graphically. Regression analysis may be performed.

A detailed statistical analysis plan will be finalised prior to data base lock, although it is anticipated that this will be the first stage in reporting and subsequent post-hoc analyses will be performed and documented as being post-hoc.

Figure 1 illustrates some of these derived variables.

[figure not shown]

Figure 1: Stylised diagram of an artery to demonstrate the various PET indices that are derived from the regions of interest (ROI) placed on the vessel. A circular ROI is drawn to encompass the vessel wall on each contiguous axial segment. Each axial segment then provides two numbers: a mean and a maximal value for the FDG uptake within that segment, expressed as the TBR. The MeanMean TBR is the averaged Mean TBR values from each artery. The MeanMax TBR is the averaged Max TBR values from each artery. The most diseased segment (MDS) is centred on the darkest red segment, defined as having the highest maximal TBR value in the entire artery. When averaged with the segments immediately above and below it, these three segments yield the MDS. Example values and their derivations are provided in the lowest row

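### The logistic model named for slice-incidence variables makes no allowance for correlation between slices of one participant; fitted to slice counts, it gives intervals that are too narrow

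*Protocol*

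**What the plan says.** Protocol section 16.1 lists five kinds of PET variable, introduced by "Within each vessel and participant visit the following variables will be derived". Items 3 and 4 are "Incidence of slices with max-TBR > 1.6" and "Incidence of slices with mean-TBR > 1.6". The other items (maxima, whole-vessel means, most diseased segment) are continuous.

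The section splits the descriptive summaries the same way. Continuous endpoints get means and standard deviations, whereas "Summary statistics for incidence or categorical variables are percentage, count and n", shown in the form p% (x/n).

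For inference, change from baseline goes to an ANCOVA "with fixed effects for the treatment and adjustment for baseline value and treatment centre". Treatment-effect estimates "will be provided with 95% confidence intervals and p-values". The next step is: "Comparisons of proportions will be handled using a similar approach based on logistic regression to estimate odd ratios". No participant effect, robust variance or overdispersion term is mentioned. Section 11.9 randomises participants 1:1, stratified by centre.

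**The concern.** A logistic model needs a count of events out of a number of trials. For the PET variables, section 16.1 defines no yes/no event per participant: no rule says how many slices above 1.6 make a participant positive. The only count and denominator supplied are slices above the cut-off and slices traced. The literal reading is therefore a binomial model on slice counts.

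The legend to Figure 1 describes the slices as adjoining axial segments of one artery. They share a patient and a vessel, so they cannot be presumed independent, while treatment is assigned to the participant. A binomial model with only treatment, baseline and centre terms counts each slice as new information.

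The protocol offers estimates with 95% intervals as its main product, and section 16.4 justifies the sample size by interval width. Section 16.1 also hypothesises that the drug acts only on tissue already inflamed, and the threshold-based incidences bear on that directly. An interval of false width would mislead on a question the trial was set up to examine.

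**Working it through.** **The plan's own precision figure.** Section 16.4 gives SD 0.3, 30 per arm, and a 90% chance of a half-width of 0.17 or less. The half-width is q × s × √(2/30), where 58 s²/0.3² is chi-square on 58 df.
- With q = 1.96, the value at s = 0.3 is 0.152, the 90th percentile is 0.169, and the chance of 0.17 or less is 90.8%.
- With q = t(58) = 2.002, these are 0.155, 0.173 and 86.1%.

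The figure is reproduced with the normal quantile, and to rounding with t. It concerns endpoints on the continuous TBR scale and is not disputed here.

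**Inputs for the slice incidences.** From the documents: 60 participants, 30 per arm, two centres, a model with treatment, baseline and centre, and a 95% level. Not in the documents, hence assumed: slices per vessel (m), correlation between slices (ICC), correlation between baseline and follow-up, and the average proportion of slices above 1.6 (taken as about one half).

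**Step 1: no covariates.** The design effect is DE = 1 + (m − 1) × ICC. The model's standard error is short by √DE, and the true error of a nominal 5% test is 2 × [1 − Φ(1.96/√DE)].
- m = 10, ICC = 0.05: DE = 1.45, √DE = 1.20, true error 10%.
- m = 20, ICC = 0.3: DE = 6.7, √DE = 2.59, true error 45%.
- m = 50, ICC = 0.5: DE = 25.5, √DE = 5.05, true error 70%.

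**Step 2: with the specified covariates.** Baseline adjustment absorbs part of the between-participant variation, so Step 1 overstates the problem for the model in section 16.1. Null trials were simulated, 600 per setting. Participant log-odds had SD s = 0.7, 1.2 or 1.8. The latent ICC is s²/(s² + 3.29), which gives 0.13, 0.30 and 0.50. Baseline and follow-up log-odds were correlated 0.5 or 0.8. A binomial logistic model with treatment, baseline and centre was fitted to the slice counts. Each cell shows the rejection rate at nominal 5%, then the factor by which the standard error is short (square root of the Pearson dispersion).

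| m | Latent ICC | Correlation 0.5 | Correlation 0.8 |
|---|---|---|---|
| 10 | 0.13 | 12.8%, 1.3 | 11.7%, 1.3 |
| 10 | 0.30 | 23.2%, 1.7 | 18.8%, 1.5 |
| 10 | 0.50 | 33.2%, 1.9 | 26.2%, 1.7 |
| 20 | 0.13 | 24.7%, 1.6 | 18.2%, 1.5 |
| 20 | 0.30 | 37.7%, 2.1 | 28.8%, 1.8 |
| 20 | 0.50 | 44.5%, 2.6 | 36.7%, 2.2 |
| 40 | 0.13 | 34.3%, 2.0 | 23.8%, 1.7 |
| 40 | 0.30 | 50.8%, 2.9 | 36.5%, 2.3 |
| 40 | 0.50 | 60.3%, 3.6 | 46.8%, 2.8 |

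**Step 3: the same data analysed properly.** With a Pearson overdispersion scale, rejection was 4.0% to 6.0%. With an ANCOVA of each participant's proportion on treatment, baseline proportion and centre, it was 3.8% to 6.0%. The simulation error around 5% is √(0.05 × 0.95/600) = 0.9 percentage points, so both agree with the nominal level.

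**The case against.** A reader might infer that the protocol prescribes ordinary logistic regression with slices taken as independent. It does not say so. Neither the slice as unit nor independence is stated; both are inferred from the terms listed and from silence on clustering. The sentence would also fit a quasi-binomial, robust, GEE or mixed logistic model.

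A participant-level reading has some support. The variables are derived once per vessel and participant visit, summaries of change from baseline are promised for all of them, and no matching of slices between visits is described. A per-participant percentage could go straight into the ANCOVA. In addition, section 16.1 announces a detailed statistical analysis plan and section 16.3 defers details of derived endpoints. A variance estimator is often settled there.

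These points rule out saying that the protocol mandates an invalid analysis. They do not remove the problem. The protocol goes beyond leaving detail open: it sends proportions to a named model class with named covariates, separates incidence from the continuous variables, and defines no participant-level binary event for PET. Followed literally, that yields intervals that are too narrow.

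A reader might also take the unadjusted design effect as the size of the error. With 20 to 80 slices and ICC 0.1 to 0.5, for example, it gives a 1.7- to 6.4-fold shortfall. That ignores the baseline adjustment that section 16.1 specifies, and should not be the headline.

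Finally, the trial is exploratory, does not emphasise formal testing, and has other variables aimed at inflamed tissue (the index vessel and the most diseased segment). This lowers the severity. It does not excuse an interval that fails its stated coverage, since estimation is the declared purpose.

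**Conclusion.** Wrong as written, moderate severity. As specified, the logistic model makes no allowance for correlation between slices within a participant. If it is fitted to slice counts, the intervals and p-values for the two incidence variables are too narrow.

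The direction is certain for any positive correlation. The size is not, because it rests entirely on assumed slice counts and correlations. Over 10 to 40 slices and latent ICC 0.13 to 0.5, with baseline adjustment, standard errors are short by about 1.3- to 3.6-fold and false rejection is about 12% to 60%. Nothing in the documents supports a single figure within that range.

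The point is confined to derived variables 3 and 4. The continuous PET variables give one value per participant and vessel, go to ANCOVA and are unaffected, as is section 16.4.

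**What to change.** Add one sentence to section 16.1, carried into the analysis plan, stating that slice incidence is analysed with the participant as the unit. The simplest form is an ANCOVA of each participant's percentage of slices above 1.6, adjusted for baseline percentage and centre. If an odds ratio is wanted, name a quasi-binomial model with one record per participant, or a robust GEE logistic model clustered on participant. Reserve plain logistic regression for variables that are yes/no per participant, and say whether n in the x/n summary counts slices or participants.

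No extra data or participants are needed. The cost is wider intervals for these two variables, by about the same 1.3- to 3.6-fold under the assumptions above, in exchange for coverage close to the stated 95%.

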## 16.2 Analysis Populations

**Inflammation Population:** All participants who provide baseline (V3) and post-dose (V9) scans but excluding those taking systemic steroids within 4 weeks prior to V9 will be included in the primary statistical analysis population. This population will be used in the evaluation of inflammation data.

**Safety Population:** All participants who receive at least one dose of trial drug will be included in the safety population. Randomized participants will only be excluded if there is clear documented evidence of failure to take any trial medication. Participants in the

Safety Population will be classified according to the treatment received. All safety summaries will be based on the Safety Population.

Pharmacodynamic Population: All participants who provide baseline and V8 pharmacodynamic (PD) data will be included in the PD population. This population will be used in the evaluation of PD.

MRI Population: All participants who provide baseline V3 and V9 MRI data will be included in the MRI population. This population will be used in the evaluation of MRI data.

### **16.3 Derived and Transformed Data**

Details of the derived endpoints will be provided in the Reporting and Analysis Plan. As this is an exploratory trial, any data transformations may be data-driven; i.e., based on a preliminary examination of the data, but wherever possible, will be detailed in the Reporting and Analysis Plan.

### **16.4 Number of Participants to be enrolled**

A sufficient number of participants will be enrolled so that approximately 60 participants who fulfil the primary statistical analysis population as described in Section 16.2 (approximately 30 participants per arm) complete the trial. Sample size is based in part on feasibility.

As an exploratory trial a formal power calculation is inappropriate. The analysis will focus on estimating the differences between treatments and will provide 95% confidence intervals of the form  $x \pm y$ , where  $x$  is the estimate and  $y$  is the confidence interval half-width. A smaller value of the half-width is desirable as it gives greater precision to the trial's conclusions. The value of the half-width depends, on the SD of the endpoint under consideration, the number of participants and an element of chance variation.

Based on the results of a previous GSK trial, PM1111138 "A double-blind, placebo-controlled, parallel group trial to evaluate the effects of two regimens of GW856553, over a period of 3 month, on in-vivo macrophage activity, as assessed by FDG-PET/CT imaging, in the carotid arteries and aorta of patients with established atherosclerosis" a SD of around 0.3 is estimated in many of the endpoints on the TBR scale that were considered. Under this assumption, with 30 participants per arm, there is a chance of 90% of achieving a half-width of 0.17 or less.

Such precision will be meaningful for drawing conclusion. Moreover a sample size of 30 participants per arm will provide enough data to be able to check assumptions behind the statistical analyses.

